#### Data assessment and data management

The study design is illustrated in Fig. 1. At the beginning of the study, after signing the informed consent forms, the parents caring for a child with rare diseases will fill in the baseline questionnaires and participate in the structured clinical interviews, SCID-I about themselves and K-SADS-PL about their child/children. All children aged 10 years and older will also be asked to complete this diagnostic process if possible. As soon as all documents are complete, the family will be randomized into one of four groups. The research staff will subsequently inform the family about their group assignment and provide feedback on the results of the diagnostic interviews.

**Fig. 1 Fig1:**
[figure not shown]
Study design

If the family is assigned to the intervention group, the therapist who carries out the CARE-FAM and/or WEP-CARE program will be informed, and the start of the intervention will be initiated. If the family is assigned to the control group, no further treatment will be provided within the CARE-FAM study.

At 6 (T2), 12 (T3) and 18 (T4) months after randomization, the families will be contacted again by the research staff. The majority of questionnaires and diagnostic interviews for all three follow-up assessments are the same as at the baseline assessment. Furthermore, after 18 (T4) months external medical data (e.g. treatment data) and cost data from the participating health insurance companies is requested.

For quality assurance, site visits will be conducted in all study centers by principal investigators of CTC North to monitor study progress and compliance with the predetermined regulations of the study.

Study data of each study center will be collected and managed by the study center in Hamburg. The study center Hamburg will receive the original and scanned files from all other study centers. The electronic file will remain in the respective study center. Data will be collected on paper and entered into the electronic case report form (eCRF) provided by secuTrial®, which is designed by CTC North. This data entry system will be password-protected and accessible only to the database managers and study team. To ensure complete and accurate data, visual inspection of the data collected on paper will be carried out before data entry. Trained personnel will carry out the data collection via double entry. Afterwards a third person will review the double data entry. In cooperation with CTC North automated rules for detecting inconsistencies in the data will be integrated and validated by a defined Data Validation Plan.

All study-related information will be stored securely at the respective study center. All records that contain names or other personal identifiers, such as informed consent forms, will be stored separately from study records identified by code numbers. The coordinating study center will oversee the intra-study data sharing process.

All study outcomes, will be published in peer-reviewed journals and presented at scientific conferences. Authorship will be based on the eligibility criteria defined by the International Committee of Medical Journal Editors. All papers and abstracts must be approved by the coordinating center in Hamburg before submission.

Any change to the protocol which may impact the conduct of the study (e.g. study design, patient population, sample sizes, study procedures) will require a formal amendment. Any such amendment will be agreed upon by Deutsches Zentrum für Luft- und Raumfahrt (DLR), and approved by the local Ethics Committee (Medical Chamber Hamburg) prior to implementation.

In this study, serious adverse events are defined as (a) death or suicide, (b) self-harm, (c) hospitalization or prolongation of existing hospitalization, or (d) distress or attendance at emergency department, whereas adverse events are defined as any deterioration of the mental state and any perception of the patient to have been adversely affected. Serious adverse events and adverse events will be compiled after the families have given consent and enrolled in the study and will be recorded by the study personnel.

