## Background

A disease is considered rare if no more than 5 out of 10,000 people are affected by it [1]. It is estimated that approximately 2 million children and adolescents in Germany live with one of up to 8000 different rare diseases [2]. While rare diseases comprise a heterogeneous group of complex disease patterns, they are usually characterized by a severe, chronic course, limited life expectancy and occurrence of symptoms already in early childhood [3]. Disease management requires a high degree of support and care from parents and siblings leading to high demands on the family [4]. Children and adolescents with rare diseases, their siblings and parents are therefore often under high physical and psychological stress [5]. Parents of chronically ill children are at high risk for clinical depression and anxiety [6, 7] and affected children themselves are at increased risk for externalizing and internalizing behavioral, as well as developmental disorders [8]. Siblings grow up in a living environment that is characterized by the care and medical treatment of their sick sibling. They are often involved in the responsibility for their siblings, in nursing, and technical medical tasks. Therefore, it is not surprising that siblings also exhibit an increased risk for behavioral disorders [9, 10]. Despite their high level of stress, all family members must “function” to a high degree and organize care for the sick child. Even under great stress and with psychological symptoms, parents usually do not seek conventional psychosocial care, e.g. psychotherapy for their children or themselves, because this would require additional time and emotional resources [11]. Although psychosocial care in the form of conciliar consultation is available in German children’s hospitals, this cannot offer effective, comprehensive treatment.

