### Participants

Participants will be recruited from in- and outpatient departments of pediatric hospitals in the 17 participating study centers. Pediatricians will be asked to inform their rare disease patients and the patients’ families about the project and encourage them to contact the study team. Once families have expressed their interest to participate in the study, a member of the research staff will approach the respective families and inform them about the project.

Once all participating family members have provided written informed consent, the baseline questionnaires and interviews will be conducted. An overview of the inclusion and exclusion criteria is given in Table 1. Families with at least one child with a rare disease aged from 0 to 21 years will be included. Families can decide for themselves which family members want to participate; however, all family members will be encouraged to take part in the study. Both couples as well as single parents can take part in the study. Participation is not limited to biological parents; adoptive parents, stepparents as well as foster parents may enter in the study. To compensate for their time conducting the interviews and filling in the questionnaires, each family will receive a financial compensation of €50 if all follow-up assessments are completed.

**Table 1 Tab1:** Inclusion and exclusion criteria

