### Research procedure

In order to be able to realistically recruit the sample, recruitment will be extended to several clinics and outpatient clinics. Patients will be recruited at the above-mentioned cooperating clinics and outpatient clinics, where approved therapists can treat study patients. The project staff members will review the weekly admissions and discharge lists and/or participate in the outpatient clinic/ward conferences of the cooperating institutions. The project staff will inform eligible patients and their parents about the study and ask them to participate in the study. If informed consent is given, diagnostics will be carried out.

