The primary outcome, parent’s psychopathology measured by the SCID-I, is evaluated according to the intention-treat (ITT) principle. The ITT population consists of all randomized families for which baseline documentation is available. As the members of a family live under common conditions and interact with each other, cluster effects can be assumed. Thus, the inferential statistics are performed with mixed models. The primary outcome is binary (diagnosis according to SCID-I yes/no). A mixed logistic regression with family and family member as random effects, recruitment center, therapy group (2 factors: 1st factor CARE-FAM yes/no, 2nd factor WEP-CARE yes/no), and time as fixed effects within the ITT population of all initially conspicuous parents is performed. The interactions between time and the therapy groups is determined. If they are not significant, they are eliminated from the model. Missing values are treated by direct imputation to allow an ITT analysis. Under the assumption of two stochastically independent interventions, the contrast of each group factor at T4 is tested at the 5% level (two-sided hypothesis). Thereby, each intervention can prove to be effective on its own. Only these results are interpreted in a confirmatory manner. In an additional analysis, we test the assumption of independence by examining the interaction between both therapy group factors. The primary analysis is repeated in the per protocol population, which consists of all families with at least three sessions in CARE-FAM or WEP-CARE. To assess the effect of the interventions within specific subgroups, the following subgroup analyses are performed regarding study center, disease of children, age of the children, and disease of parents. In a series of sensitivity analyses, missing values are imputed by different approaches as last observation carried forward, multiple imputation, worst- and best-case imputations. Secondary outcomes are investigated exploratively without adjustment for multiplicity in the ITT population. The analysis strategy for the secondary, binary outcomes is the same as in the primary analysis. For secondary, continuous outcomes, linear mixed models with differences to baseline as outcome, family and family member as random effects and the same fixed effects as in the above-mentioned model and respective baseline value as covariate are examined. The safety outcomes are determined using frequency tables and if possible, with mixed logistic regression analogue to the primary analysis. Odds ratios or adjusted means, their 95% confidence interval, and *p* values are reported according to the CONSORT statement. Interim analyses are not planned. Statistical analyses will be carried out with standard statistical software.

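### The serious adverse event definition mixes all-cause medical events with psychological harm and does not say whose events count, so disease-driven events can dilute the safety comparison

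*Protocol article*

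**What the plan says.** The definition stands near the end of the Protocol article's section on data assessment and data management. It begins "serious adverse events are defined as (a) death or suicide, (b) self-harm" and goes on to "c) hospitalization or prolongation of existing hospitalization, or (d) distress or attendance at emergency department". No item is limited by cause, planned status or relation to mental health. The same sentence then gives ordinary adverse events a psychological definition: "adverse events are defined as any deterioration of the mental state and any perception of the patient to have been adversely affected". Both kinds of event "will be compiled after the families have given consent and enrolled in the study and will be recorded by the study personnel". Whether parents, affected children, siblings or all of them are meant is not stated.

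The population is described in three places. The Background says that rare diseases usually have a "severe, chronic course, limited life expectancy and occurrence of symptoms already in early childhood". Under Participants: "Participants will be recruited from in- and outpatient departments of pediatric hospitals in the 17 participating study centers". Under Research procedure: "The project staff members will review the weekly admissions and discharge lists", and/or attend clinic and ward conferences.

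The Data analysis section gives the safety analysis in one sentence: "The safety outcomes are determined using frequency tables and if possible, with mixed logistic regression analogue to the primary analysis". The Study setting section adds that SAEs are discussed at the monthly steering committee and yearly advisory board meetings.

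**The concern.** The two event classes rest on different ideas. An adverse event is mental deterioration or perceived harm, which is what a psychosocial programme could plausibly cause. An SAE is any hospital stay, prolongation, emergency visit or death, whatever its cause. In families with a severely ill child, followed for 18 months and partly found through admission lists, somatic events of this kind are foreseeable in all four groups and have little to do with the interventions.

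Two things follow. First, if a rare psychological harm is compared within an outcome that also contains common disease events, a true excess becomes hard to see, and a finding of no difference in hospitalization or in any SAE would say little about psychological safety. Second, because the text does not say whose events count, one site may report a child's planned stay and another only the parents' events, so the background itself may vary between sites.

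**Working it through.** **1. What component tables can separate.**

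| Component | Psychological event | Disease-driven event in the same class |
|---|---|---|
| (a) death or suicide | suicide | death from the rare disease |
| (b) self-harm | self-harm | none obvious |
| (c) hospitalization or prolongation | psychiatric admission of a parent, child or sibling | planned or acute somatic admission, longer stay |
| (d) distress or emergency attendance | distress, psychiatric emergency | somatic emergency of the child |

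Only (b) is clean. For (a), (c) and (d), the psychological part can be isolated only if cause and person are recorded.

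**2. Is there a figure to reproduce?** No. The article states no safety event rate and no safety power. The one input taken from it is the number of families per level of each factor: 155 per group × 2 = 310.

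**3. Illustration of dilution.** These inputs are assumptions: psychological SAE in q0 = 2% versus q1 = 7% of families, and an independent disease-driven SAE in a proportion h of families, equal at both levels. If all events are pooled to one yes/no outcome per family,

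p = 1 − (1 − q)(1 − h), so the difference is (1 − h)(q1 − q0).

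Power for a two-sided 5% test of two proportions is Φ[(d − 1.96·se0)/se1], where d is the difference, se0 = √(2·p̄(1 − p̄)/310) and se1 = √((p0(1 − p0) + p1(1 − p1))/310).

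- h = 0: d = 0.050, se0 = 0.01665, se1 = 0.01653; (0.050 − 0.0326)/0.01653 = 1.05; power 85%.
- h = 10%: p0 = 1 − 0.98 × 0.90 = 0.118, p1 = 1 − 0.93 × 0.90 = 0.163, d = 0.045, se0 = 0.02791, se1 = 0.02785; (0.045 − 0.0547)/0.02785 = −0.35; power 36%.

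| h | Observed rates | Odds ratio | Power |
|---|---|---|---|
| 0 | 2.0% v 7.0% | 3.69 | 85% |
| 10% | 11.8% v 16.3% | 1.46 | 36% |
| 20% | 21.6% v 25.6% | 1.25 | 22% |
| 40% | 41.2% v 44.2% | 1.13 | 11% |
| 60% | 60.8% v 62.8% | 1.09 | 7% |

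The formula ignores rejections in the wrong direction. Counting them gives 12% and 8% in the last two rows. From h = 0 to 10%, the difference shrinks only from 5.0 to 4.5 points. Most of the loss comes from the added variance.

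**4. Other assumed harm rates, 310 per level.**

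| Psychological SAE | h = 0 | h = 10% | h = 30% |
|---|---|---|---|
| 2% v 6% | 72% | 26% | 11% |
| 3% v 8% | 78% | 35% | 15% |
| 5% v 10% | 66% | 32% | 15% |
| 5% v 12% | 88% | 54% | 25% |

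If 20% of families are lost (310 × 0.8 = 248 per level), the 2% v 7% case gives 77% at h = 0, 30% at h = 10% and 10% at h = 40%. For small excesses even the undiluted outcome is weak: 31% for 2% v 4% and 43% for 1% v 3%.

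**The case against.** The strongest reply is that the article never says the components are pooled. It lists four lettered items, speaks of safety outcomes in the plural, puts frequency tables first and models only if possible. Self-harm would then have its own row. This stands. A reader might infer from the definition that every event counts equally in one any-SAE comparison, and the text does not support that. The power figures describe that analysis if it is run. What the reply leaves open is the mixing inside (a), (c) and (d).

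Psychological harm also has other channels. Adverse events are defined by mental deterioration and perceived harm. Blinded raters interview parents and assess children at baseline, 6, 12 and 18 months, and symptom questionnaires are given at the same visits. This stands too. It rules out the inference that a real excess of harm would go unseen and be reported as no safety difference.

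Whose events enter the model is open. The primary model has family and family member as random effects and is fitted in initially conspicuous parents. If the safety model copies that, children's admissions stay out and the dilution is smaller. Recruitment through outpatient departments also lowers the background.

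Finally, all-cause criteria avoid subjective attribution where families know their group, and rules on relatedness or planned stays may be in the full protocol or analysis plan. Their absence from the article is therefore not the point here. The point is the definition that the article does state. The all-cause choice is a good reason to keep recording every event, but it does not prevent classifying them afterwards.

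**Conclusion.** The concern holds in a limited form. As stated, the SAE definition combines all-cause deaths, admissions and emergency visits with suicide, self-harm and distress, leaves open whose events count, and is applied to families with a severely ill child recruited through hospitals. Any comparison of hospitalization, emergency attendance or any SAE can therefore be diluted, and component tables alone do not cure it.

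The direction does not depend on the assumed rates; the size does. For 2% versus 7% of families and 310 families per level, power falls from 85% to 36% at a 10% background and to 11% at 40%. This assumes pooling at family level and independent background events at equal rates in the compared groups. It would be tempting to say that disease events swamp the signal, but the documents give no rates that would show it. An equal background also creates no false difference between randomized groups. Efficacy is unaffected, and the safety analysis is not confirmatory. The change should be made because it is cheap and makes the safety result interpretable.

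**What to change.** Keep recording and tabulating all SAEs as defined. In addition:

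1. State whose events count: parents, affected children, siblings, or all participating members.
2. Classify each event, blind to allocation, by family member and by cause: psychological or psychiatric, versus somatic or related to the rare disease, with planned admissions marked.
3. Add a compared safety outcome of suicide, self-harm, or psychiatric hospitalization or emergency attendance, placed beside the all-cause tables and not in their stead.
4. Show non-suicide deaths and somatic events separately in the tables, and use the same split in the listings for the steering committee and advisory board.

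The cost is two extra fields on the SAE form and revised wording for the safety tables. Events already recorded must be classified retrospectively, with some judgement on cause. The added outcome may still have little power for small excesses, so estimates with confidence intervals will be more informative than tests.

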### Data analysis

For both, primary and secondary outcomes, descriptive statistics are presented separated by treatment groups on family level as well as on child and parents’ level. Categorical variables are summarized by absolute and relative frequencies. Continuous variables are summarized by mean and standard deviation (SD) or by median, quartiles and/or interquartile range (IQR), as appropriate. The number of available observations and the number of missing observations are reported separately for treatment groups.

The primary outcome, parent’s psychopathology measured by the SCID-I, is evaluated according to the intention-treat (ITT) principle. The ITT population consists of all randomized families for which baseline documentation is available. As the members of a family live under common conditions and interact with each other, cluster effects can be assumed. Thus, the inferential statistics are performed with mixed models. The primary outcome is binary (diagnosis according to SCID-I yes/no). A mixed logistic regression with family and family member as random effects, recruitment center, therapy group (2 factors: 1st factor CARE-FAM yes/no, 2nd factor WEP-CARE yes/no), and time as fixed effects within the ITT population of all initially conspicuous parents is performed. The interactions between time and the therapy groups is determined. If they are not significant, they are eliminated from the model. Missing values are treated by direct imputation to allow an ITT analysis. Under the assumption of two stochastically independent interventions, the contrast of each group factor at T4 is tested at the 5% level (two-sided hypothesis). Thereby, each intervention can prove to be effective on its own. Only these results are interpreted in a confirmatory manner. In an additional analysis, we test the assumption of independence by examining the interaction between both therapy group factors. The primary analysis is repeated in the per protocol population, which consists of all families with at least three sessions in CARE-FAM or WEP-CARE. To assess the effect of the interventions within specific subgroups, the following subgroup analyses are performed regarding study center, disease of children, age of the children, and disease of parents. In a series of sensitivity analyses, missing values are imputed by different approaches as last observation carried forward, multiple imputation, worst- and best-case imputations. Secondary outcomes are investigated exploratively without adjustment for multiplicity in the ITT population. The analysis strategy for the secondary, binary outcomes is the same as in the primary analysis. For secondary, continuous outcomes, linear mixed models with differences to baseline as outcome, family and family member as random effects and the same fixed effects as in the above-mentioned model and respective baseline value as covariate are examined. The safety outcomes are determined using frequency tables and if possible, with mixed logistic regression analogue to the primary analysis. Odds ratios or adjusted means, their 95% confidence interval, and *p* values are reported according to the CONSORT statement. Interim analyses are not planned. Statistical analyses will be carried out with standard statistical software.

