#### Sample size

Sample size calculation was carried out with the software PASS 2015, using two independent proportions and is based on the assumed increase in the proportion of non-conspicuous parent among the initially conspicuous parents according to SCID-I criteria between the patients treated with CARE-FAM and patients that did not receive CARE-FAM at18 months after randomization. Additionally, we assume the same effect size between patients with and without WEP-CARE. Furthermore, we suppose that the two interventions work independently of each other. Given a power of 80% and a type I error rate of 5% (two-sided hypothesis), 74 initially conspicuous parents per treatment combination group (296 in total) are needed to detect a difference of 11.2% (91.2% of the CARE-FAM patients and 80% of the non-CARE-FAM patients) in the proportion of non-conspicuous parents between both groups. We further assume that at the beginning of the study 30% of the parents are conspicuous. So, at the end of the study, a total of 988 parents must be available for evaluation. Additionally, we expect a dropout rate of 20% between baseline and follow up. To compensate for this, a total of 1236 parents must be recruited. This means that a total of 618 (rounded up to 620) families (310 per stratum CARE-FAM yes/no, 155 families per group of the four randomization groups: CARE-FAM only, WEP-CARE only, combination, no study intervention) has to be included in the trial.

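### The confirmatory primary model adjusts for no baseline severity measure, although graded severity scores are collected before randomisation; adding one would be a low-cost gain in efficiency

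*Protocol article*

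**What the plan says.** All references are to the protocol article.

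- **Primary model (Data analysis).** The model is listed term by term: "A mixed logistic regression with family and family member as random effects, recruitment center, therapy group" as two yes/no factors, and time. The population is restricted to parents with a SCID-I diagnosis at baseline. No baseline covariate is listed. Binary secondary outcomes follow the same strategy.
- **Continuous secondary outcomes (same section).** Linear mixed models of the change from baseline use the same fixed effects, "and respective baseline value as covariate are examined".
- **What is measured beforehand.** Table 2 schedules BSI, PHQ-D and GAF for parents at the pre-randomisation visit. Under Data assessment and data management: "As soon as all documents are complete, the family will be randomized into one of four groups". Randomization and blinding adds that every participating parent in a randomised family has had the standardised diagnostics. It also names recruitment centre as the only stratification factor.
- **Planning assumptions (Sample size).** "74 initially conspicuous parents per treatment combination group (296 in total) are needed to detect a difference of 11.2" percentage points, that is "91.2% of the CARE-FAM patients and 80% of the non-CARE-FAM patients". This is a comparison of two independent proportions and assumes no gain from a covariate.

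**The concern.** The exploratory continuous analyses are adjusted for baseline, and the one confirmatory analysis is not. The natural baseline value for the primary outcome cannot be used, because selecting parents with a diagnosis fixes it at yes for all of them. Graded scores that might predict who still has a diagnosis at 18 months are available and unused.

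The stake is precision. Few parents are expected to remain conspicuous at 18 months, and planned power has no reserve above 80%. In a logistic model, leaving out a covariate that predicts the outcome lowers the power for the treatment effect. Severity within this subset, assumed to be 30% of parents, is also balanced only by chance.

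**Working it through.** **Inputs from the protocol.** Two-sided alpha 5%; power 80%; 91.2% versus 80% without a diagnosis at 18 months; 74 parents per cell, so 2 × 74 = 148 per level of each factor.

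**Input not in the protocol.** The strength of association between baseline severity and 18-month SCID-I status. It is varied below as an assumption.

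**1. The plan's own figure.**

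- Pooled proportion: (0.912 + 0.80)/2 = 0.856.
- SE under the null: √(2 × 0.856 × 0.144/148) = 0.0408.
- SE under the alternative: √((0.912 × 0.088 + 0.80 × 0.20)/148) = 0.0403.
- Power = Φ((0.112 − 1.96 × 0.0408)/0.0403) = Φ(0.79) = 78.7%.
- Exact binomial enumeration at 148 per level gives 79.99%.

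The stated 80% reproduces as an unadjusted figure.

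**2. Expected events.** 148 × 0.20 + 148 × 0.088 = 29.6 + 13.0 ≈ 43 parents still conspicuous among 296.

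**3. Effect of adding one severity score.** Trials were simulated with one outcome per parent, 148 versus 148, and a standard normal severity score. Intercepts were set so that the marginal rates stay at 80% and 91.2%. The test is a logistic Wald test with and without the score. AUC and r (correlation of score with outcome) refer to the 80% group. There were 4,000 runs per row, except 3,000 in the row for coefficient 1.3, for which r was not computed.

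| Assumed coefficient per SD | AUC | r | Unadjusted | Adjusted |
|---|---|---|---|---|
| 0 | 0.50 | 0 | 78.2% | 78.0% |
| 0.5 | 0.635 | 0.19 | 78.6% | 79.8% |
| 0.8 | 0.703 | 0.29 | 78.9% | 81.7% |
| 1.0 | 0.744 | 0.35 | 79.5% | 83.5% |
| 1.3 | 0.79 | – | 79.5% | 86.1% |
| 1.5 | 0.822 | 0.46 | 78.9% | 87.4% |

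Further runs at the weak end (3,000 each) gave 78.6% to 79.2% at AUC 0.58 and 80.1% to 80.9% at AUC 0.64. The Monte Carlo standard error of one power estimate is √(0.8 × 0.2/4000) ≈ 0.6 points, or 0.7 points with 3,000 runs.

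**4. Cost of extra terms.** With 17 centres as fixed effects (2,000 runs), power for coefficients 0, 0.8, 1.0 and 1.3 was 80, 78, 81 and 77% unadjusted and 80, 80, 84 and 84% adjusted. A second covariate with no prognostic value changed power by at most 0.7 points. Type I error stayed between 4.4% and 5.9% across all models.

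**5. In terms of sample size.** By the approximation N × (1 − r²), r = 0.3 gives 296 × 0.91 ≈ 269, equivalent to about 27 of the 296 parents. At r = 0.2 it gives 296 × 0.96 ≈ 284, about 12 parents.

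**6. Effect measure.** The unadjusted odds ratio is (0.912/0.088)/(0.80/0.20) = 2.59. With the same marginal rates and r = 0.29, the odds ratio conditional on severity is 2.79.

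**The case against.** The strongest reply is that nothing here is wrong. A randomised comparison adjusted for centre, the two factors and time is valid, and the 80% power claim neither assumes nor needs a covariate. That stands, and it limits the point to efficiency. It could be added that covariates are detail for an analysis plan that is not shown. That carries less weight, because the article lists the model's terms and writes a baseline covariate into one class of model and not the other.

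The size of the gain is also open to challenge. The protocol gives no association between BSI or GAF and later SCID-I status. Weak prediction is plausible: every analysed parent already meets diagnostic criteria, the outcome is 18 months away, and 80% are expected to recover without CARE-FAM. The gain is then about a point or less. The simulations also leave out family clustering and repeated visits, so they indicate the relative gain and not the power of the planned model. Both objections stand. The family-member random effect, however, does not recover this precision for a contrast between families.

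Three stronger readings are tempting, and the protocol does not support them.

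- **Severity was left out because baseline SCID-I is constant.** The protocol gives no reason. It follows only that baseline SCID-I cannot be the covariate.
- **The primary and secondary models contradict each other.** The secondary models adjust for the same scale's baseline value, and the primary outcome has no usable equivalent.
- **Chance imbalance in severity biases the result.** Randomisation and the test's type I error already allow for it. Adjustment would improve precision.

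A claim that adjustment would make up for the power lost to clustering also fails, because no intraclass correlation is given from which to work out that loss.

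**Conclusion.** The point holds as an efficiency improvement, not as an error of validity. The confirmatory model uses no baseline severity measure, baseline SCID-I cannot fill that role in the analysed subset, and suitable graded scores are collected before randomisation.

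At the planned size and rates, adjustment would move power from about 79% by roughly 0 to 1 point for a weak predictor (AUC up to 0.64) and by about 2 to 7 points at AUC 0.70 to 0.79. With no prognostic value there is no material loss. These figures rest on assumed prognostic strength and on one independent outcome per parent. The case for the change is that its downside is negligible; the protocol does not establish that a large gain is available.

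**What to change.** Before unblinding, add one clause to the primary analysis naming a single continuous baseline severity score, for example the BSI total, as a fixed covariate in the primary model and its sensitivity analyses. GAF may be added.

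Two accompanying statements are needed:

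- **A simple rule for a missing baseline score.** Baseline diagnostics precede randomisation, but the ITT definition itself requires that baseline documentation be available, so occasional gaps should be expected.
- **A statement that the reported odds ratio is conditional on baseline severity.** The mixed model's odds ratio is already conditional on its random effects. Adjustment adds a further condition and changes its value slightly (2.59 against 2.79 in the example above).

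The cost is one or two degrees of freedom, beside the 16 already used for centre. No new data and no change to trial conduct are needed.
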